# Impact of a diagnostic strategy for appendicitis in children with acute abdominal pain in primary care: study protocol for a hybrid type 1 cluster randomised controlled trial

**DOI:** 10.1186/s41512-026-00234-x

**Published:** 2026-08-13

**Keywords:** Appendicitis, Primary care, Children, Clinical prediction rule, C-reactive protein

## Abstract

**Background:**

Children with acute abdominal pain pose a diagnostic challenge for general practitioners (GPs), as it can be difficult to distinguish appendicitis from self-limiting conditions due to overlapping symptoms. To support GPs, a diagnostic strategy for appendicitis was developed that integrates an externally validated prediction rule with C-reactive protein point-of-care testing (CRP POCT) and risk-based management advice. This study will compare the impact of this diagnostic strategy to usual care in children with acute abdominal pain in primary care in terms of: (i) clinical effectiveness, (ii) cost-effectiveness, and (iii) implementation potential.

**Methods:**

We will conduct a pragmatic, hybrid type 1 effectiveness-implementation, cluster randomised controlled trial in Dutch general practice. Children aged 4–18 years with acute (≤ 7 days) abdominal pain will be included. GP practices will be randomly allocated to either: (i) use of the diagnostic strategy for appendicitis, or (ii) usual care. In the intervention group, children are stratified into low, medium, or high risk for appendicitis based on a seven-item prediction rule including symptoms and signs. Management advice is tailored to appendicitis risk: safety netting for low-risk, immediate referral for high-risk, or CRP POCT for medium-risk (CRP < 10 mg/L: safety netting; CRP 10–50 mg/L: reassessment or immediate referral (based on GPs’ clinical judgement and parent/child preference); CRP ≥ 50 mg/L: immediate referral). The primary outcome is referral efficiency (proportion of non-referrals amongst patients with no appendicitis during 30 days follow-up). Secondary outcomes include safety, proportion of children with CRP POCT, proportion of children with planned reassessment, child anxiety, patient satisfaction, quality of life, and costs. A parallel process evaluation will assess implementation outcomes, including the reach, adoption, implementation, and maintenance of the diagnostic strategy. We aim to include 566 children without appendicitis to determine an improvement of efficiency from 88% to 95%.

**Discussion:**

We hypothesise that use of the diagnostic strategy will reduce referrals without increasing delayed diagnoses of appendicitis, compared to usual care in children presenting with acute abdominal pain in primary care. This may ultimately result in better patient outcomes, lower costs, and reduced health care resource use.

**Trial registration:**

ClinicalTrials.gov: NCT06762275 (registration date: 2024/12/03).

**Supplementary Information:**

The online version contains supplementary material available at 10.1186/s41512-026-00234-x.

## Background

Acute abdominal pain is a common reason for doctor consultations in children, accounting for nearly 10% of childhood visits in primary care [1]. More than 90% of these children have self-limiting conditions such as gastroenteritis or constipation [2, 3], whereas 5% have acute appendicitis, the prime reason for referral to secondary care in this population [2, 4–6]. Prompt recognition and referral of children with appendicitis by the general practitioner (GP) is crucial, as perforation occurs in 18% of cases [2] and is associated with high morbidity, including increased risk of postoperative complications (39%), pelvic abscess formation (53%), readmissions (14%) and prolonged hospitalisation [7–12]. Yet timely diagnosis of appendicitis is challenging in primary care, as early symptoms can be atypical and often overlap with those of benign conditions [5, 13, 14]. Moreover, current GP guidelines provide limited support, as they lack explicit referral criteria for appendicitis and do not recommend the use of C-reactive protein point-of-care testing (CRP POCT) due to insufficient evidence [4]. Consequently, 19% of children with appendicitis are not referred during the initial GP consultation, while 70% of those who are referred do not have appendicitis, which can lead to avoidable anxiety, healthcare utilisation and costs [2, 3, 15–18].

Although several prediction rules for identifying appendicitis in children exist in secondary care [13, 19], only one has been developed and validated in a primary care setting [20]. This rule, based on seven routinely available symptoms and signs, stratifies children into low-, medium-, or high-risk groups for appendicitis. External validation demonstrated good discrimination (c-statistic 0.90; 95% CI 0.89–0.92) and good calibration [20]. An additional study showed that CRP adds diagnostic value beyond symptoms and signs and may improve decision making in children with diagnostic uncertainty, corresponding with the medium-risk group of the prediction rule [21].

A low-cost diagnostic strategy combining the prediction rule with CRP POCT for medium-risk children (Fig. 1) could reduce referrals by providing risk-based management advice and is easy for GPs to use during consultations. However, its impact in everyday practice needs to be established before widespread implementation [22–25]. To address this knowledge gap, we designed a trial comparing the impact of the diagnostic strategy for appendicitis with usual care in children presenting with acute abdominal pain in primary care, in terms of: (i) clinical effectiveness, (ii) cost-effectiveness, and (iii) implementation potential.

**Fig. 1 Fig1:**
[figure not shown]
Diagnostic strategy for acute appendicitis, including the probability of appendicitis per risk group. AA, acute appendicitis; CRP, C-reactive protein; POCT, point-of-care testing

## Methods

### Study design

The ISAAK study (*Impact van een diagnostische Strategie voor Acute Appendicitis bij Kinderen*) is a pragmatic, hybrid type 1 effectiveness-implementation [26], superiority, cluster randomised controlled trial (RCT) in Dutch general practice, with GP practices as the unit of randomisation (Fig. 2).

Recruitment of GP practices started in November 2024, and the first child was enrolled in March 2025. The inclusion of children will continue until the required sample size is reached, which is expected in January 2028 (planned end date including 3 months follow-up: April 1st 2028).

The study protocol has been reviewed and approved by the Central Ethical Review Committee of the University Medical Center Groningen (UMCG) (METC number: 2022/399).

**Fig. 2 Fig2:**
[figure not shown]
Flow-chart of the study design. GP, general practitioner

### Study population

Children aged 4 to 18 years, presenting to the GP with acute (onset ≤ 7 days) abdominal pain are eligible for inclusion. Children with prior appendectomy, abdominal pain caused by trauma or those who are pregnant are excluded.

### Recruitment

GP practices from three primary care networks (*Academic General Practitioner Development Network of UMCG*, *Julius General Practitioners Network of University Medical Center Utrecht* and *Extramural Leiden University Medical Center Academic Network*) and from the study team’s network are invited to participate by email. Participating GPs and GP trainees will recruit eligible children during office-hour consultations. Additionally, GP assistants will perform a monthly search of the primary care electronic health records (EHRs) of enlisted children using selected International Classification of Primary Care (ICPC) codes to identify and invite eligible children who have been missed by the GP (Supplementary 1).

Figure 3 outlines the recruitment process of children. During or after the consultation, the GP informs eligible children and/or parents about the study and asks consent to share contact and consultation data with the study team via an electronic case report form (CRF).

**Fig. 3 Fig3:**
[figure not shown]
Recruitment process including data collection timeline. Anonymised baseline data (age, sex, date of baseline consultation, and randomisation group) will be collected for children who meet the inclusion criteria but do not provide consent to share contact details, or who object to participation after contact

Upon retrieval of the contact and consultation data, the study team sends an email to the parent or child, including a patient information letter and informed consent form (Supplementary 2). Patients provide written consent for participation in the study, which includes completing questionnaires, and provide separate consent for collecting relevant data from the child’s EHR. If there is no response within seven days, the study team follows up by phone to provide further study details and to answer any questions.

### Randomisation, allocation and blinding

GP practices are randomly allocated to the intervention or control group using computer-generated 1:1 permuted-block randomisation with randomly varying block sizes, with stratification based on practice size (above or below 5000 patients). The randomisation is performed by an independent methodologist ([name], PhD). Blinding of GPs and patients is neither feasible nor appropriate in this pragmatic study [27]. Additionally, blinding of outcome assessors is not possible. However, data analysis will be conducted blinded to group allocation, meaning that the data analysts will be unaware of participant assignment until the analysis is complete. During the annual visits to participating general practices, the research team will verify any GP staffing changes. If a GP transfers from an intervention to a control practice or vice versa, their participation will be discontinued to avoid contamination.

### Control: usual care

GPs in the control group provide usual care at their own discretion. They are advised, but not obliged, to follow the NHG guideline ‘Abdominal pain in children’, which lacks specific referral criteria for appendicitis. The guideline advises suspicion of appendicitis in children with right lower quadrant pain, tenderness, and fever, and referral in case of peritonitis signs or abnormal bowel sounds. When in doubt, GPs are advised to plan a reassessment. CRP testing is not recommended due to lack of evidence. During a site initiation visit prior to the start of the study, the researchers present a summary of the NHG guideline to GPs. No additional education and/or materials are provided.

### Intervention: diagnostic strategy for appendicitis

GPs in the intervention group use a diagnostic strategy for appendicitis that integrates an externally validated seven-item prediction rule with CRP POCT and risk-based management advice. The prediction rule consists of routinely available signs and symptoms, each assigned a point score (Table 1).

**Table 1 Tab1:** Clinical prediction rule for acute appendicitis

Predictor	Point score
Male sex	2
Nausea/vomiting	2
Pain duration < 24 h	1
Pain duration 24–48 h	2
Elevated temperature ≥ 37.3˚ C	1
Abnormal bowel sounds (absent, tinkling or high-pitched)	1
Right lower quadrant tenderness	5
Peritoneal irritation (abdominal rigidity, guarding, rebound tenderness and/or pain with jarring movements)	4

Based on the total score of the prediction rule, children are stratified into three risk groups: low (0–7 points), medium (8–13 points) and high risk (≥ 14 points) for appendicitis. A sensitivity and specificity for appendicitis of ≥ 95% correspond with the lower (7 points) and upper (14 points) cut-offs, respectively [20]. Management advice is tailored to appendicitis risk (Fig. 1): safety netting is advised for low-risk children, while immediate referral is recommended for those at high-risk. For children in the medium-risk group, GPs are instructed to perform CRP POCT. Based on the CRP value, the strategy recommends either safety netting (CRP < 10 mg/L), reassessment or immediate referral depending on the GP’s clinical judgment and parent/child preference (CRP 10–50 mg/L), or immediate referral (CRP ≥ 50 mg/L). The reassessment is considered a continuation of the initial consultation and includes a repeat clinical assessment and, if indicated, CRP POCT, and should take place later the same day or, if not feasible, the following morning. Cut-offs for CRP were derived from previous primary care research, where CRP ≥ 10 mg/L showed 0.87 (95% CI 0.77–0.94) sensitivity for appendicitis, increasing to 1.00 (95% CI 0.89-1.00) after 48 h, and CRP ≥ 50 mg/L demonstrated 0.94 (95% CI 0.93–0.96) specificity [21].

CRP POCT is performed in line with Dutch laboratory standards. For all participating practices, we will record both the availability and the type of CRP POCT device. Since all CRP POCT devices used in Dutch general practice have good accuracy and comparability [28–30], each practice will use its own device. GPs are instructed to follow the diagnostic strategy as much as possible, but are informed that they may deviate from the recommended management when deemed necessary. During the site initiation visit, the researchers give a brief presentation of the NHG guideline and the diagnostic strategy to GPs. Each GP also receives a pocket card containing the diagnostic strategy.

### Implementation strategies

As shown in previous research, diagnostic strategies are often not used or used incorrectly by GPs, which can reduce efficiency and increase failure rates [31–33]. We therefore complemented the diagnostic strategy with targeted implementation strategies to improve adherence [34–38]. Prior to study conduct, we identified barriers and facilitators through qualitative research, literature, and stakeholder input using the Consolidated Framework for Implementation Research (CFIR) (Supplementary 3) [39]. Based on these findings, we identified implementation strategies using the CFIR-Expert Recommendations for Implementing Change (ERIC) Matching Tool and developed these into study-specific strategies (Supplementary 4). The two main strategies are online training and a clinical decision tool integrated in the primary care EHR system, based on the ERIC strategies: developing educational materials, promoting adaptability and reminders for clinicians [40–44].

#### Clinical decision support tool integrated in primary care EHR system

Participating GPs receive an electronic clinical decision support tool integrating the diagnostic strategy into the primary care EHR system. The tool was developed in collaboration with software developers (ExpertDoc and Health Base). It is available in two formats, depending on the practice’s type of EHR system. Both versions were tested and approved by six academic and non-academic GPs from the project team.

For GP practices using Medicom as EHR system, the diagnostic strategy is directly integrated into the EHR. It appears in real time as a pop-up when an ICPC-code for gastrointestinal symptoms (D.xx) is entered for children aged 4 to 18 years, enabling the GP to record the presence of signs and symptoms, and CRP POCT value if needed, and receive tailored recommendations.

For non-Medicom practices, direct integration into the EHR was not feasible. Instead, GPs access the tool via a REDCap (Research Electronic Data Capture) link, either through a desktop application or the NHGDoc Classic button. This button, available in five Dutch EHR systems (CGM, OmniHIS, Promedico ASP, microHIS, Bricks), turns yellow when an ICPC D.xx code has been entered, directing the GP to the REDCap tool.

### Data collection

GPs will complete a baseline CRF for eligible children during the initial consultation, which contains the inclusion and exclusion criteria, contact details of the parent or child, and questions on whether CRP POCT or referral was performed, and why. For GPs in the intervention group, the diagnostic strategy is also included (Supplementary 6).

Medical record data will be collected for all participating children using a standardized form (Supplementary 7). Parents and/or children will complete electronic questionnaires on secondary outcomes via REDCap. Parents complete questionnaires for children ≤ 7 years. For children aged 8–15 years, both the child and parent complete questionnaires separately. Children ≥ 16 years complete all questionnaires independently, except for the cost questionnaire, which they fill out together with a parent.

Questionnaires are emailed at 30 days and 3 months after baseline. Automated reminders from REDCap are sent after 5 days and 10 days. If questionnaires remain incomplete after 10 days, the study team follows up by phone.

All study-related and participant information is stored securely at the study site on institutional servers of the University of Groningen and the University Medical Center Groningen, accessible only to authorized researchers.

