#### Secondary outcomes

#### Safety

Safety is defined as the proportion of children with appendicitis who are referred during the initial GP consultation or planned reassessment (Table 3).

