#### Costs

Medical and societal costs will be assessed using adapted versions of the iMTA Productivity Cost Questionnaire (iPCQ) and the iMTA Medical Consumption Questionnaire (iMCQ), completed at 30 days and 3 months follow-up. Parents (for children ≤ 15 years) or parents and child (≥ 16 years) will report healthcare use, out-of-pocket expenses, and productivity losses (absence from work). Additionally, researchers will extract information regarding healthcare consumption from children’s medical records (e.g. CRP POCT, GP visits, referrals, hospital admissions, operative and non-operative management in hospital, including antibiotic therapy). All standard-of-care, including all types of healthcare usage, is included in the cost-effectiveness analysis. Medical equipment costs for CRP POCT will be calculated according to the Dutch costing manual, including depreciation, interest, and maintenance costs. Annualized equipment costs will be allocated per procedure based on the expected annual number of measurements on the machine.

The units measured will be monetised according to guidelines of the National Healthcare Institute of the Netherlands [52].

**Table 3 Tab3:** Definitions of safety and efficiency

	Appendicitis +	Appendicitis -
Referred ^a^	a	b
Not referred	c	d

Definitions: Safety (sensitivity) = a / (a + c). Efficiency (specificity) = d / (b + d). The sample size calculation is based on the denominator of the efficiency outcome (b + d)

^a^ Referred at the initial GP consultation for acute abdominal pain or at planned reassessment

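### Efficiency and safety both depend on whether a later referral was made at a planned reassessment, a label judged from records by assessors who know the arm

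*Protocol article*

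**What the plan says.** Safety is defined as "the proportion of children with appendicitis who are referred during the initial GP consultation or planned reassessment". Footnote a to Table 3 defines the referred row for all four cells as "Referred at the initial GP consultation for acute abdominal pain or at planned reassessment", so the same label also decides efficiency, the primary outcome.

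Table 2 gives medical records as the only source for efficiency and safety. For the separate secondary outcome of planned reassessment it gives CRF management data plus medical records, with no restriction by arm.

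The Data collection section says that the baseline CRF holds "questions on whether CRP POCT or referral was performed, and why. For GPs in the intervention group, the diagnostic strategy is also included". It also states: "Medical record data will be collected for all participating children using a standardized form". The CRF and the extraction form are Supplementary 6 and 7, which are not at hand.

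The section on randomisation, allocation and blinding says: "Additionally, blinding of outcome assessors is not possible". It gives no reason specific to assessors. Data analysts are to be blinded.

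**The concern.** A referral at a planned reassessment goes in the referred row. A referral at an unplanned return goes in the not-referred row. Nothing else about the child need differ, so the word planned decides the cell.

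The article describes the label differently for the two arms. The intervention section treats reassessment as part of the initial consultation and gives it a timing. The usual-care section says only that GPs are advised to plan one when in doubt, with no timing. An assessor reading a control note about a second visit may therefore have less to go on, and knows which arm the note comes from.

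The Discussion's conclusion, that referrals fall without more delayed diagnoses, rests on both outcomes. A lean in coding does not affect them alike. Calling a later referral unplanned lowers an arm's safety if the child has appendicitis, and raises that arm's efficiency if the child does not.

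**Working it through.** **1. The plan's own figure.** Inputs from Sample size considerations: 88% v 95%, two-sided 5%, power 80%, cluster size 3, intraclass correlation 0.01. The pooled two-proportion formula gives 248 per arm. The design effect is 1 + (3 − 1) × 0.01 = 1.02, and 248 × 1.02 = 253 per arm, 506 in total (stated: 510). Allowing for 10% loss, 510 / 0.90 = 567 (stated: 566). Power at 255 / 1.02 = 250 effective children per arm is 80.3%. The sample size reproduces and is not in question.

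**2. Weight of one label for safety.** The Background gives a 5% prevalence of appendicitis. Then 566 × 0.05 / 0.95 = 29.8 cases, or 14.9 per arm. One relabelled case moves an arm's safety by 100 / 14.9 = 6.7 points. If prevalence among enrolled children were 8% or 10% (assumptions), there would be 24.6 or 31.4 cases per arm and the shift would be 4.1 or 3.2 points.

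**3. How many cases could be affected.** The Background reports that under current care "19% of children with appendicitis are not referred during the initial GP consultation". Each such child who is later referred is classified by the label: 0.19 × 15 = about 3 per arm.

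**4. Illustration for safety.** The article does not say what share of these children are referred at a planned reassessment (s), or what share of plans would go unrecognised (m). Assume error in the control arm only, none in the intervention arm. Control safety = 0.81 + 0.19 × s × (1 − m).

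| s | m = 0 | m = 0.25 | m = 0.50 | Shift |
|---|---|---|---|---|
| 0.50 | 90.5% | 88.1% | 85.8% | 2.4 to 4.8 points |
| 0.75 | 95.3% | 91.7% | 88.1% | 3.6 to 7.1 points |

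With 15 cases, these shifts amount to 0.4 to 1.1 children.

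**5. Illustration for efficiency.** Assume that 20% of referrals of children without appendicitis occur at reassessment, and that 25% to 50% of those are coded unplanned in one arm only.
- Control arm: 12% × 0.20 × 0.25 to 0.50 = 0.6 to 1.2 points. Control efficiency reads 88.6% to 89.2%, and power against 95% falls from 80.3% to 74.3% or 67.2%.
- Intervention arm: 5% × 0.20 × 0.25 to 0.50 = 0.25 to 0.5 points. Intervention efficiency reads 95.25% to 95.5%, so the difference is slightly overstated.

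The direction therefore depends on which arm the error falls in, and the article does not settle that.

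**6. Can the label be coded blind?** Staff who visit practices will know the arm. Deciding whether a dated visit had been planned is a separate step. It can be done from an extract by someone who sees neither practice, arm nor strategy output. The statement that assessor blinding is not possible is too strong for that step.

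**The case against.** A reader might infer more: that the control CRF does not capture planned reassessment, that the intervention CRF leaves a structured trace of it, and that safety is therefore ascertained unequally. The documents do not support this.
- Table 2 takes safety and efficiency from medical records, not from the CRF, and one standardised form is used for all children.
- For planned reassessment, Table 2 names the CRF without restriction by arm, and the outcome is to be recorded in each randomised group.
- The sentence on CRF content is a summary of a form that is not shown.
- No passage describes a field in the strategy for a planned reassessment. The CRP 10–50 mg/L branch leads to reassessment or referral, and GPs may deviate, so the advice does not prove a plan.

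Other points against the concern also carry weight. The bias figures rest on assumed inputs. The half-width of the 95% interval for the safety difference at 15 per arm is about 1.96 × √(2 × 0.81 × 0.19 / 15) = 28 points, ignoring clustering, so imprecision dominates. The Discussion already calls for caution on safety. Appendicitis itself is diagnosed from specialist findings, so masking that label would add little.

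What remains is narrower. The caution in the Discussion concerns power, not classification by assessors who know the arm. A common extraction form standardises what is read, not the judgement on whether a visit was planned. Under-recognition in control records would be conservative for efficiency, but the same error in the intervention arm would not be.

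**Conclusion.** The concern holds as a risk of differential classification in the primary outcome and in safety. It arises from one label that needs judgement and is coded with knowledge of the arm. It does not hold as a finding that the arms are ascertained unequally.

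Size and direction are unknown. The firmest figure is that one relabelled case moves an arm's safety by about 7 points at 5% prevalence (about 3 to 4 points if prevalence is 8% to 10%). The shifts of 2.4 to 7.1 points in safety and 0.25 to 1.2 points in efficiency are illustrations that depend on assumed shares and on error in one arm only.

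Separately, the description of the CRF and Table 2 do not match on whether the CRF covers planned reassessment, and should be reconciled.

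**What to change.** 1. Replace the statement that assessor blinding is not possible with wording such as: *Extraction is unblinded. For children referred or diagnosed with appendicitis within 30 days, whether a later visit was planned is coded by one written rule, the same in both arms, from dated extracts with practice, arm and strategy output removed, by a team member not involved in practice visits.* The same rule serves children found through the monthly record search, who may have no CRF from the consultation itself.
2. Add a sensitivity analysis of efficiency and safety that does not use the label. It would count all referrals within one common period after the initial consultation in both arms, with the period fixed before unblinding. This is an analysis rule and changes no care.
3. Reconcile the Data collection section with Table 2 on whether the CRF asks about planned reassessment in both arms. A new CRF item should not be added by default: it may duplicate an existing one, and it could prompt reassessment in the usual-care arm, where reassessment is itself an outcome.

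**Cost.** Expected referrals without appendicitis are 283 × 0.12 + 283 × 0.05 = 48. With about 30 appendicitis cases that makes 78, plus an unknown number referred at unplanned visits, so roughly 100 extracts for existing staff. Masking may be incomplete where the notes reveal the arm. Enrolment is expected to run to January 2028, and coding from dated extracts can also cover children already enrolled.
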